### Objectives:

The main objective of this trial is to evaluate the effectiveness of cognitive behavioral therapy for insomnia integrated in best-evidence pain management (CBTi-BEPM) versus BEPM-only for reducing pain intensity at 12 months post-intervention. Additionally, on an exploratory basis, we will examine if CBTi-BEPM versus BEPM-only can improve other pain-related and sleep-related outcomes, physical activity, depressive symptoms and anxiety, and quality of life, extending up to 12-months after treatment.

### Design:

The study comprised a multicentre, triple-blind, randomised, controlled, two-arm (1:1) trial. Treatment outcomes will be assessed at baseline, at post-intervention, and at 3, 6 and 12 months follow-up. At the 3 and 6-month follow-up, online self-reported outcome data was collected.

### Study population:

One-hundred-twenty patients with nonspecific chronic spinal pain (nCSP) and comorbid insomnia will be recruited. Eligibility criteria are outlined in the table 1.

| Inclusion                                                                                                                                                                                                 | Exclusion                                                                               |
|-----------------------------------------------------------------------------------------------------------------------------------------------------------------------------------------------------------|-----------------------------------------------------------------------------------------|
| Nonspecific spinal pain for at least 3 months' duration, at least 3 days/week                                                                                                                             | Severe underlying sleep pathology (identified through baseline data of polysomnography) |
| Aged between 18 and 65 years                                                                                                                                                                              | Neuropathic pain                                                                        |
| Seeking care because of neck pain or low back pain                                                                                                                                                        | Chronic widespread pain syndromes                                                       |
| Native Dutch Speaker                                                                                                                                                                                      | Shift workers                                                                           |
| Having insomnia: in the absence of other intrinsic sleep-disorders and shift work, insomnia is defined as > 30 min of sleep latency and/or minutes awake after sleep onset for >3 days/week for >6 months | Being pregnant or pregnancy (including given birth) in the preceding year               |
| Not starting new treatments or medication and continuing their usual care 6 weeks prior to and during study participation (to obtain steady state)                                                        | Thoracic pain in absence of neck or low back pain                                       |
| Refraining from analgesics, caffeine, alcohol, or nicotine in the previous 48h of the assessments                                                                                                         | History of specific spinal surgery (e.g., surgery for spinal stenosis)                  |
| Nonspecific failed back surgery >3 years are permitted                                                                                                                                                    | Body Mass Index over 30                                                                 |
| Not undertaking exercises (>3 MET) in the 3 days before the assessment                                                                                                                                    | Presence of a current clinical depression diagnosed by a doctor                         |

Table 1. In- and exclusion criteria

### Details polysomnography for eligibility screening

An overnight home polysomnography (PSG) measurement using the Alice PDX portable sleep diagnostic system (Philips Respironics, Murrysville, PA, USA) was completed to verify study eligibility with regard to the exclusion of specific sleep disorders. Obstructive sleep apnea was defined when the apnea-hypopnea index was over 15 and periodic leg movement disorder was defined as a periodic limb movement index over 15. The scoring of these indices followed the American Academy of Sleep Medicine Manual for Scoring of Sleep and Associated events guidelines.

### Recruitment strategy:

Adults with nCSP and comorbid insomnia are recruited via flyers in the participating Universities and University Hospitals, primary care practices, occupational health services, public places, via advertisements and social media.

**Sample size calculation:**

Sample size (n=120) is calculated using G\*Power based on the effects on pain in a pilot study (Cohen's  $f = 0.25$ ,  $\alpha = .05$ ,  $\text{power} = .80$ ), accounted for F-tests and 20% loss to follow-up after one year.

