Descriptive statistics were used to report the demographic variables and baseline characteristics of the participating nCSP patients per intervention group, with means (Standard Deviation [SD], range and Inter Quartile Range [IQR]) for continuous variables and frequency (%) for categorical variables. All analyses were by intention-to-treat, with all participants included in the analysis according to their randomly allocated treatment. All analyses were performed in SPSS 24.0. For average pain intensity (primary outcome) and for all explorative, secondary outcomes, the change between baseline and other time points was calculated:  $\Delta 1 = \text{baseline (T0)} - \text{post-treatment (T1)}$ ;  $\Delta 2 = \text{T0} - \text{3-month follow-up (T2)}$ ;  $\Delta 3 = \text{T0} - \text{6-month follow-up (T3)}$ ; and  $\Delta 4 = \text{T0} - \text{12-month follow-up (T4)}$ . Differences in the change in average pain intensity at 12-month follow-up (primary outcome at primary endpoint) and at the other time points (immediately post-intervention, and at 3- and 6-month follow-up) were analysed using a random-intercept fixed slope linear mixed model (incl. LSD post-hoc analyses), which was applied using an unstructured covariance matrix. Linear mixed models are a likelihood-based estimation procedure whereby likely values for missing data are estimated from information contained in the observed data, resulting in non-biased estimates providing data are missing at random. The model included treatment, time, and treatment\*time as fixed effects together with a random intercept for each patient. Model assumptions were evaluated visually using residual plots. Mean group differences (95% confidence interval) at the different time points and their p-values and effect sizes for the intervention comparisons are reported. Level of significance for the primary outcome was set at  $\alpha .05$ . Effect sizes were calculated as Cohen's d (interpreted as  $>1.3$  = very large;  $.80-1.29$  = large,  $.50-.79$  = medium,  $.20-.49$  = small,  $<.20$

= negligible). The same analysis was used to evaluate the explorative, secondary outcomes at the different time points.

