Sensitivity analyses were performed using the same analysis, including the baseline level of average pain intensity (for all pain-related outcomes) and the baseline level of insomnia severity (for sleep-related outcomes) as confounding factor. The analysis of dropout and loss-to-follow-up was conducted by categorizing the entire cohort into two subsets, distinguished by their adherence or discontinuation from the trial (which also included loss-to-follow-up). Comparative assessment of baseline characteristics and data between the two groups was accomplished utilizing a t-test or its non-parametric equivalent.

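### The stated 80% power (n = 120, f = 0.25, 20% loss) cannot be reproduced from the inputs given and is not supported for the unadjusted 12-month difference in change

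*Combined protocol and SAP*

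**What the plan says.** **Sample size calculation.** "Sample size (n=120) is calculated using" G*Power, with Cohen's f = 0.25 taken from a pilot study, alpha .05 and power .80, "accounted for F-tests and 20% loss to follow-up after one year". The section gives no further inputs.

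**Study population and Design.** "One-hundred-twenty patients with nonspecific chronic spinal pain (nCSP) and comorbid insomnia will be recruited", in a "randomised, controlled, two-arm (1:1) trial".

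**Statistical analysis plan, item 7.** The primary test is identified by "Differences in the change in average pain intensity at 12-month follow-up (primary outcome at primary endpoint". The model is a linear mixed model for the change scores, with treatment, time and their interaction as "fixed effects together with a random intercept for each patient". Baseline pain is not in this model. It enters only later: "Sensitivity analyses were performed using the same analysis, including the baseline level of average pain intensity". Item 6 leaves missing data to the mixed model.

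**The concern.** A sample size statement should let a reader recover n from its inputs, for the contrast that decides the trial. Here the inputs, taken at face value for two groups, lead to a larger number than 120. The tests that do lead to about 120 are not the planned primary test.

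This is the only power statement for the single primary outcome and time point. If power for the 12-month contrast is below 80%, the chance of missing the planned effect is greater than the 20% a reader will assume. A null result would then be read as stronger evidence against an added effect of CBTi on pain than it is.

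**Working it through.** **Inputs from the documents.** N = 120 at 1:1; f = 0.25; alpha = .05; target power .80; 20% loss, so 120 × 0.8 = 96 evaluable (48 per arm). For two equal groups d = 2f = 0.50.

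**Step 1. Try to reproduce 120 from the stated inputs alone.** Two-group F-test, noncentrality λ = f²N = 0.0625 N, degrees of freedom 1 and N − 2.

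| N evaluable | λ | Power |
|---|---|---|
| 96 | 6.0 | 0.679 |
| 120 (no loss) | 7.5 | 0.775 |
| 128 | 8.0 | 0.801 |

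The test needs 128 evaluable patients, and 128 / 0.8 = 160 randomised. The figure of 120 is not reproduced. Loss to follow-up does not explain the gap, because 120 with no loss still falls short of 80%. With 96 evaluable, 80% power is reached at f ≈ 0.289, that is d ≈ 0.58.

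**Step 2. Look for a test that does give about 120.** Each route below adds inputs that the documents do not state.

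- *Repeated measures, between factors*, λ = f²N·m / (1 + (m − 1)r), with m measurements correlated at r:
  - m = 2, r = 0.5: 98 evaluable, 98 / 0.8 = 122.5, so 123 randomised.
  - m = 3, r = 0.6: 96 evaluable, 96 / 0.8 = 120.
  - m = 4, r = 0.7: 100 evaluable, 100 / 0.8 = 125.
- *Baseline-adjusted test (ANCOVA)*, λ = f²N / (1 − r²): r = 0.5 gives 98 evaluable, so 123 randomised. At N = 96, λ = 6 / 0.75 = 8.0 and power is 79.9%.
- *Repeated measures, within-between interaction*: 14 to 46 patients under the usual convention (m = 2 to 5, r = 0.3 to 0.7). With λ = f²N(m − 1) it needs 128, 80, 60 and 50 for m = 2 to 5, or 160, 100, 75 and 63 after dividing by 0.8. None is 120.

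The first route tests a group effect averaged over visits. The second is planned only as a sensitivity analysis. Neither is the primary contrast.

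**Step 3. Power of the planned 12-month contrast if f is on the change-score SD.**

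- Completers only: 67.9% (Step 1).
- With partial data: suppose the 24 dropouts contribute either the first or the first three of the four post-baseline visits, with a common correlation ρ among change scores (assumed). The effective N for the 12-month mean is the inverse of its variance from the combined information matrix.

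| ρ (assumed) | Effective N | Power |
|---|---|---|
| 0.3 | 97.8 to 99.4 | 68.7% to 69.4% |
| 0.5 | 101.1 to 103.8 | 70.2% to 71.3% |
| 0.7 | 106.4 to 109.4 | 72.4% to 73.6% |

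**Step 4. Power if f is on the raw-score SD.** With equal variances at both visits, the change score has SD √(2(1 − r)) times the raw SD, so λ = 6 / (2(1 − r)) at N = 96. Here r is the baseline-to-12-month correlation (assumed).

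| r | λ | Complete-case power |
|---|---|---|
| 0.3 | 4.29 | 54% |
| 0.4 | 5.00 | 60% |
| 0.5 | 6.00 | 68% |
| 0.6 | 7.50 | 77% |
| 0.7 | 10.00 | 88% |

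80% is reached at r ≈ 0.63.

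**Step 5. If the primary model were baseline-adjusted, with f on the raw-score SD.** λ = 6 / (1 − r²) gives power of 72%, 80% and 92% for r = 0.3, 0.5 and 0.7.

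**The case against.** The strongest reply is that the plan never says the calculation was an unadjusted two-group F-test. It says only that F-tests were used, and does not say whether f refers to raw scores or changes. The sponsor may hold G*Power inputs that give 120 exactly. On the raw-score reading, power reaches 80% at a correlation of about 0.63, or about 0.60 if partial data are used and changes correlate at 0.5. The mixed model also means that dropouts are not wholly lost. Finally, the SAP requires mean differences with 95% confidence intervals at each time point, which limits over-reading of a null result.

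Much of this stands. A reader might infer that true power is 68% and the risk of missing the effect is 32%. The documents do not support that as an unconditional statement: the miss risk runs from 12% to 46% over the correlations in Step 4. A reader might also infer that the sponsor must have powered a visit-averaged effect. That is not established either, because a baseline-adjusted test with r of about 0.5 gives nearly the same n.

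The reply does not rescue the stated 80%. Partial data lift power on the change-score reading only to about 74%. Every route to 80% needs a correlation that the documents do not give, and the routes giving about 120 test something other than the planned primary contrast. Confidence intervals help interpret the result but do not correct the planning claim.

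**Conclusion.** The concern holds in conditional form. The combination of n = 120, f = 0.25, alpha .05, 80% power and 20% loss cannot be reproduced from the stated inputs, and 80% is unsupported for the unadjusted 12-month difference in change.

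The size of the shortfall depends on the meaning of f. On the change-score scale it is about 12 percentage points for completers and about 6 to 11 points with partial data, the latter assuming ρ of 0.3 to 0.7. Even with no loss it is 2.5 points. On the raw-score scale the plan could be well below or somewhat above 80%, depending on an unstated correlation. The finding is an unsupported power claim with missing inputs; it does not show that the sponsor's own G*Power run was wrong.

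**What to change.** Keep n = 120 and revise the sample size paragraph in two ways.

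1. State which G*Power F-test was run, the number of measurements, the correlation, and whether f = 0.25 refers to the raw-score or the change-score SD.
2. Restate power for the 12-month contrast under the planned model as a conditional figure. If f is on the change-score scale, suitable wording is: *With 120 randomised and 96 evaluable at 12 months, power for the between-group difference in change is about 68% for d = 0.50 on the change score, and up to about 74% if partial data contribute (assumed correlation among changes up to 0.7); 80% power with 96 evaluable applies to d of about 0.58.* If f is on the raw-score scale, give the Step 4 range with the assumed correlation.

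If the sponsor instead makes the primary model baseline-adjusted, the paragraph can state about 80% power for d = 0.50 on the raw-score SD assuming r = 0.5, with 72% at r = 0.3 and 92% at r = 0.7.

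The cost is a rewritten paragraph and, on most readings, a less favourable stated power. No extra patients are needed. Restating the power leaves the analysis unchanged; only the baseline-adjusted option alters the primary model.

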**Randomisation:**

Randomization is computer-generated at the Biostatistics Unit of Ghent University by an independent investigator, uninvolved in any other trial aspects. Block randomisation was used (ratio 1:1) for the two treatment centres (Ghent; Brussels) separately, with stratification for sex (male; female) and dominant pain location (neck; low back). The randomisation is performed by an independent researcher, who places papers indicating group assignment in sequentially numbered, opaque, and sealed envelopes. Concealed allocation is ensured since the independent researcher – who will be the only person with access to the envelopes – writes the initials of the selected participants on the appropriate envelope before opening them.

**Outcome measures:**Primary outcome:

The primary clinical outcome is defined as average pain intensity, assessed using the Brief Pain Inventory (BPI) item 'average pain intensity in the last 24h' evaluated on an 11-point NRS (30% decrease is clinically important).

Explorative, secondary pain-related outcomes:

- BPI worst pain intensity (last 24h) on an 11-point (0–10) numeric rating scale
- BPI least pain intensity (last 24h) on an 11-point (0–10) numeric rating scale
- BPI pain intensity now on an 11-point (0–10) numeric rating scale
- BPI pain severity: the mean of the four pain intensity items
- BPI pain interference: the BPI also evaluates the pain interference related to general activity, walking, work, mood, enjoyment of life, relation with others and sleep on separate 11-point numeric rating scales.
- The Central Sensitisation Inventory (CSI; cut-off value of 40/100 to indicate the presence of central sensitization-related symptoms) to assess symptoms of central sensitisation. The CSI uses 25 statements related to current health symptoms, indicative of central sensitization (scored on a five-point Likert scale ranging from zero to four).
- Pressure pain thresholds (PPT; increase of >15% is clinically important), defined as the point of minimum pressure that induces an unpleasant sensation is assessed with a digital pressure algometer (Wagner instruments), randomly applied at the painful and two remote locations. The painful level is the trapezius muscle in neck pain patients and at L3 lumbar paravertebral muscles in low back pain patients. Remote sites are the web between the thumb and the index and the proximal one third of the calf. The threshold is determined as the mean of two consecutive measurements, with 30 s in between.

Explorative, secondary sleep-related outcomes:

- The Pittsburgh Sleep Quality Index (cut-off = 6/21; 3 points difference as clinically important) to assess self-reported perceived sleep quality. It is a 19 item scale with 1 week time interval. Its score ranges between 0 and 21 and 0 indicates no sleep difficulty and 21 indicating severe sleep difficulties.
- The Insomnia Severity Index (cut-off = 14/28; 6 points difference as clinically important) to assess self-reported insomnia severity. It is a 5-item 5-point Likert scale applying a 2 week time interval. Its scores range between 0 and 28 and 0 indicates no clinically significant insomnia and 28 indicating severe clinical insomnia.
- Dysfunctional Beliefs and Attitudes about Sleep questionnaire to assess self-reported dysfunctional beliefs and attitudes about sleep. It is a 16-item 5-point Likert scale with scores ranging between 0 and 10. Scores over 4 indicate unrealistic expectations for sleep or unrealistic thoughts about sleep.
- The Epworth Sleepiness Scale to assess self-reported sleep propensity. It is an 8-item 4-point Likert scale, with scores ranging between 0 and 24 and with 0 indicating normal daytime sleepiness and 24 indicating severe excessive daytime sleepiness.
- The Brugmann Fatigue Scale to assess self-reported fatigue severity with mental fatigue subscale and physical fatigue subscale. The score ranges from 0 to 24 and higher scores indicate a higher subjective level of fatigue.

- Objective sleep outcomes derived from one night polysomnography assessment (portable Alice PDX, Philips Respironics IncTM). Participants were asked to refrain from caffeine after lunch, smoking in the evening and alcohol as well as intensive sport for the whole day. Participants were furthermore asked to take their regular medications and not to initiate new pharmacological treatments on the day of the polysomnography. Objective sleep quantity and architecture outcomes derived from the polysomnography recording were, at each time point, time in bed, total sleep time, sleep onset latency, wake duration after sleep onset, and early morning awakening in minutes; Non-Rapid Eye Movement (nREM) and REM sleep in % of total sleep time; Sleep efficiency in %; and number of arousals. The scoring of these sleep parameters followed the American Academy of Sleep Medicine Manual for Scoring of Sleep and Associated events guidelines. The researcher who scored the polysomnography recording was blinded to group allocation.

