#### **Interventions:**

Both groups receive 18 sessions of approx. 30 minutes over 14 weeks. All sessions are delivered by physical therapists (Master of Science), and are one-on-one, individualized sessions (except for one group pain educational session of 1h) using principles of person-centred care and applying guidance towards self-management. The experimental intervention comprises 6 sessions of CBTi, integrated in 12 sessions of BEPM (i.e., CBTi-BEPM). The control intervention comprises of 18 sessions of BEPM (BEPM-only). The treatment contrast lies therefore in the 6 CBTi sessions. CBTi includes sleep education, self-monitoring of sleep patterns, time-in-bed restriction, stimulus control, sleep hygiene, cognitive restructuring, and relaxation. For details, see. BEPM includes pain neuroscience education (PNE; 3 sessions) and cognition-targeted exercise therapy. In CBTi-BEPM 9 sessions of cognition-targeted exercise therapy are provided, while in the BEPM-only intervention 15 sessions of cognition-targeted exercise therapy are provided to ensure balanced treatment arms regarding therapy/therapist exposure time. For full details on BEPM, see.

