From the sleep diary, sleep efficiency was computed as the ratio of total sleeping time to the total time spent in bed, serving as an indicator for sleep restriction therapy. Sleep efficiency represents a possible mismatch between time spent in bed and total sleep time. This therapy involves limiting the hours spent in bed as closely as possible to the actual hours of sleep (i.e. determining the sleep window). To achieve this, the time in bed was restricted to the mean sleep time of the previous week, as recorded in the sleep diary, which heightened sleep pressure. Consequently, excessive time in bed was addressed, and a mild form of sleep deprivation ensued. Importantly, the sleep window was never reduced below 5 hours per night, and the participant was not allowed to make any changes without consulting the therapist. In the long term, this approach facilitates faster sleep onset, improves sleep continuity, and results in a deeper, higher-quality sleep by stabilizing the circadian rhythm and balancing the production of melatonin and cortisol. Daytime naps were permitted, but their duration was restricted to a maximum of 15 minutes and only allowed if taken before 2 p.m.

Changes in the prescribed, restricted time in bed occurred using the following guidelines:

- Sleep efficiency = 80-85% : sleep window is retained
- Sleep efficiency < 80% : a new sleep window is determined by making the total time in bed equal to the mean total sleep time of the past week (sleep window  $\geq$  5 hours because of safety and health concerns)
- Sleep efficiency > 85% : sleep window is extended by 15 minutes

Together with an efficacy > 85% any use of sleep-related medication was phased out in agreement with the participant and in close collaboration with the general practitioner of the participant.

For participants with high levels of anxiety, an exception was permitted. This allowed them to choose their bedtime freely one night per week to avoid heightened alertness caused by stress arising from sleep restriction therapy.

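### Arousals are compared as a raw count per night, which can mislead if total sleep time differs between arms; only the CBTi arm has its time in bed restricted

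*Combined protocol and SAP*

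**What the plan says.** **Outcome.** Under Outcome measures, in the explorative sleep-related list, the protocol describes "Objective sleep outcomes derived from one night polysomnography assessment". The variables include "at each time point, time in bed, total sleep time, sleep onset latency", and the list closes with "Non-Rapid Eye Movement (nREM) and REM sleep in % of total sleep time; Sleep efficiency in %; and number of arousals". No arousals-per-hour measure is listed, and no recording length is fixed. On method the text says only: "The scoring of these sleep parameters followed the American Academy of Sleep Medicine Manual for Scoring of Sleep and Associated events guidelines".

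**Intervention.** Under Interventions, "CBTi includes sleep education, self-monitoring of sleep patterns, time-in-bed restriction, stimulus control", and "The treatment contrast lies therefore in the 6 CBTi sessions". The Behavioral therapy part of the CBTi content explains that "the time in bed was restricted to the mean sleep time of the previous week", with a floor of 5 hours and 15-minute extensions once sleep efficiency exceeds 85%. It expects some initial sleep loss and says that in the long term the approach "improves sleep continuity, and results in a deeper, higher-quality sleep".

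**Analysis.** Item 7 of the statistical analysis plan applies one linear mixed model, on change from baseline (baseline minus follow-up), to every secondary outcome. The only added covariate for sleep outcomes is baseline insomnia severity, in a sensitivity analysis. Nothing adjusts for sleep time.

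**The concern.** A count of events depends on how long the events could occur. Arousals occur during sleep, so two nights with the same fragmentation but different amounts of sleep give different counts. The trial restricts time in bed in one arm only, so a difference in sleep duration between arms is a foreseeable effect of treatment. A lower count in the CBTi-BEPM arm could then be read as more consolidated sleep when it partly reflects less sleep. Equally, an unchanged count could hide a higher arousal rate.

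Objective sleep measures are likely to be used as corroboration in a trial whose other sleep outcomes are self-reported, so the arousal result may be read as evidence of mechanism.

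A smaller matter concerns the stage variables. Two shares of the same total, with no third category, carry one piece of information, and pooling all nREM sleep leaves no measure of sleep depth.

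**Working it through.** The documents state no arousal rate, sleep time, stage distribution or standard deviation, so there is no figure of the plan's own to reproduce. Every value marked *assumed* is illustrative.

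**1. Count against rate**

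count = arousal rate (per hour of sleep) × total sleep time (hours)

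At a constant rate, the percentage change in count equals the percentage change in total sleep time. Assume 15 arousals/h and 6.5 h of sleep, so 15 × 6.5 = 97.5 arousals, with the control arm staying at that level:

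| CBTi-arm sleep (assumed) | Count | Difference | Change |
|---|---|---|---|
| 6.5 h | 97.5 | 0 | 0% |
| 6.0 h | 90.0 | −7.5 | −7.7% |
| 5.5 h | 82.5 | −15.0 | −15.4% |
| 5.0 h | 75.0 | −22.5 | −23.1% |

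The percentages do not depend on the assumed rate; the absolute differences do. For 6.5 h falling to 5.5 h, rates of 10 to 25/h give 10 to 25 fewer arousals. With change taken as baseline minus follow-up, these falls appear as positive change in the CBTi-BEPM arm.

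Two cases run the other way:

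- If the CBTi arm slept longer, say 7.0 h, the count would be 15 × 7.0 = 105, or 7.7% higher with no worse fragmentation.
- If the count stayed at 97.5 while sleep fell to 5.5 h, the rate would be 97.5 / 5.5 = 17.7/h, an 18% rise that the count does not show.

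Dividing the count by total sleep time returns 15/h in every row of the table, so the difference is zero.

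**2. Could duration alone give p < .05?**

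Take 120 less 20% loss = 96, or 48 per arm, in a two-sided two-sample comparison at 5% with assumed SDs of change in the count:

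| Difference due to duration alone | SD 25 | SD 40 | SD 60 |
|---|---|---|---|
| 7.5 arousals (30 min less sleep) | 31% | 15% | 9% |
| 15 arousals (60 min less sleep) | 84% | 45% | 23% |

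The range of 9% to 84% rests wholly on the assumed SDs and sleep deficits. It shows that the effect need not be negligible, not that it is large here.

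**3. When a difference in sleep time is plausible**

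The 3- and 6-month follow-ups collect online self-report (Design), so I infer that follow-up recordings fall post-intervention and at 12 months. Table 4 places the last CBTi session in week 10 of 14. The window grows by 15 minutes per step, and participants are not to alter it on their own. A shorter night is therefore most plausible post-intervention. By 12 months the difference may have vanished or reversed.

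**4. nREM% and REM%**

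Both use total sleep time as denominator, so nREM% = 100 − REM%. Their changes from baseline are equal and opposite, so the same linear model gives the same p-value with the sign reversed. A simulated comparison of 48 per arm gave p = 0.961 for both.

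On depth, light-to-deep nREM stages (N1/N2/N3) of 10/55/15 and 5/45/30 (assumed) both sum to nREM 80%, leaving REM 20%. The deepest stage doubles and neither listed variable moves.

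**The case against.** The strongest reply is that restriction acts on time in bed, whereas arousals accrue during sleep. The window is set to the previous week's mean sleep time, so what is removed is chiefly time awake in bed. Total sleep time may fall little, and the documents do not show by how much at either recording. This stands. A reader might infer that a shorter recording by itself lowers the count, or that the comparison is definitely biased towards CBTi-BEPM. The documents support neither: the driver is total sleep time, and the direction depends on which arm sleeps longer.

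Second, time in bed, total sleep time and efficiency are reported as well, so a reader could see shorter sleep beside fewer arousals. This is a partial safeguard. Arm means side by side do not correct the arousal estimate or its p-value.

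Third, the outcomes are exploratory, the significance level is set for the primary outcome, and no claim in the objectives rests on arousals. This also stands and limits the importance of the point.

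Fourth, reporting both stage shares is harmless redundancy, and sleep depth is not among the stated objectives. I accept this. A reader might infer that the trial is unable to demonstrate an effect it set out to test. However, deeper sleep appears in the therapy rationale, not in the protocol's or SAP's objectives, and the documents do not say whether nREM stages were scored separately. Splitting them is a choice of outcome, not the repair of an error.

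**Conclusion.** The point holds in a conditional form. The raw count confounds fragmentation with sleep duration, in a trial where one arm's time in bed is restricted and the model does not allow for sleep time. The bias favours CBTi-BEPM if that arm's total sleep time is shorter, disfavours it if longer, and is nil if the arms are equal.

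Under an assumed fall from 6.5 h to between 6.0 and 5.0 h, with the control arm unchanged, the apparent reduction is 8% to 23% with the same arousal rate. Whether any such fall occurs cannot be judged from the documents.

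That nREM% and REM% duplicate each other is certain but of little consequence. The whole point concerns exploratory outcomes; the primary pain comparison is untouched. It is worth acting on because the correction is nearly free.

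**What to change.** In the polysomnography item under Outcome measures:

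1. Add arousals per hour of total sleep time (count divided by total sleep time, both already collected) and name it as the measure for the between-group comparison. Keep the raw count as descriptive. A count model with log total sleep time as offset would serve the same purpose.
2. State that time in bed is partly set by the therapy and will be interpreted accordingly.
3. State that nREM% and REM% are complementary and count as one test.
4. Optionally, if the nREM stages were scored separately, report each as a percentage of total sleep time.

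The index should be added, not substituted for a listed outcome. The outcome and analysis text is largely in the past tense, so a swap could look like retrospective outcome switching. If results have already been seen, the addition should be labelled as post hoc.

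The cost is one derived variable and one division per recording, with no new visits or data. The index answers a narrower question than the count: how fragmented sleep is per hour, not how many arousals occur in a night. That is why the count should still be shown.
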